## Abstract

**Introduction:**

Although there are many studies on the use of convalescent plasma (CP) for treatment of COVID-19, it is not clear (1) which groups of patients may benefit, (2) what dose of plasma to give, or (3) which antibody levels the plasma should contain. Previous phase I/II studies and literature review suggest that CP should only be given to patients with viraemia, that a daily infusion should be given until the patient becomes virus free and that the neutralising antibody titre should preferably be >1:640

**Methods and analysis:**

An open randomised controlled trial enrolling patients with COVID-19, who must be SARS-CoV-2 positive in both airway and blood samples and admitted to a study hospital. Block randomisation 2:1 is to either 200 mL CP (preferably titre ≥1/640) daily for up to 10 days (until virus negative in blood) plus standard care or standard care only (control arm). The primary endpoint is mortality by day 28 after study inclusion. Secondary endpoints include mortality by day 60 and doses of plasma needed to clear viraemia. Assuming a reduced mortality of approximately 30% by the CP therapy and 85%–88% survival in the control arm, approximately 600 participants will be enrolled to the CP therapy arm and 300 participants to the control arm.

**Ethics and dissemination:**

Ethical approval has been granted by the Swedish Ethical Review Authority (reference: 2020-06277). Results from this trial will be compiled in a clinical study report, disseminated via journal articles and communicated to stakeholders.

**Trial registration number:**

NCT04649879.

Strengths and limitations of this studyA randomised trial design based on phase I and II studies that first investigated which patients to enrol (patients with viraemia) as well as how plasma should be characterised (high-neutralising antibody titre) and how it should be given (daily until viral clearance).Powered to detect a 30% mortality decrease.Clearance of viraemia is a secondary endpoint that will be very rapid to evaluate.Availability of high-titre convalescent plasma blood group matched to study participants may be a limiting factor.This is an unblinded trial.

## Introduction

COVID-19 is an ongoing pandemic caused by the SARS-CoV-2. Current treatment options are limited. Corticosteroid therapy (dexamethasone, hydrocortisone or methylprednisolone) for up to 10 days has been shown to significantly reduce mortality in severely ill patients with COVID-19, summary OR 0.66 (95% CI 0.53 to 0.82).^1 2^ Dexamethasone also reduced the risk of progression to invasive mechanical ventilation (relative risk 0.76 (0.61–0.96), p=0.021). However, no improvement was seen in patients not requiring supplemental oxygen therapy and corticosteroids were associated with prolonged viral shedding.^1 3 4^

Convalescent plasma (CP) therapy is a form of immunotherapy that has been used for the treatment and prevention of infectious diseases for more than 100 years. CP was successfully used in the treatment of SARS, Middle East respiratory syndrome and the 2019 H1N1 pandemic.^5–8^ A meta-analysis of 32 SARS and severe influenza studies showed that CP treatment was associated with a significant reduction in the pooled odds of mortality (OR 0.25; 95% CI 0.14 to 0.45).^9^ However, CP treatment did not significantly improve the survival of patients with Ebola disease.^10^ This was possibly due to a lack of data on neutralising antibody titres.

Early studies on CP therapy suggested that in COVID-19, CP should be given daily until the patient becomes virus free.^11–14^ In America, more than 70 000 patients have received CP. A safety report on 20 000 patients indicated that CP was well tolerated and not associated with severe adverse events (AE).^15^ In a cohort of 1000 patients, mortality was significantly lower in patients receiving CP with antibody titres ≥1/640 compared with patients receiving CP with lower titres if the treatment was initiated within 72 hours of admission (data available at www.fda.gov). Though the numbers treated are large and the results suggest a beneficial effect, the lack of controls leaves space for much uncertainty. Moreover, there are randomised studies reporting no beneficial effect, although CP therapy was not specifically given to patients with viraemia in these trials.^16–18^ There is thus a need for a randomised clinical trial that focuses on a population at high risk of severe COVID-19 (ie, patients with viraemia in early disease) and on which plasma to give and how (preferably neutralising antibodies of at least 1:640 and one plasma bag infused daily until clearance of viraemia occurs).

We found that viraemia on admission identifies patients at sevenfold increased risk of admission to intensive care and eightfold increased risk of death.^19^ CP treatment appeared to result in rapid viral clearance in a small case series and two randomised trials.^16 18 20^ CP appeared to be well tolerated in a phase I study in which patients only received one dose of CP and a phase II study in which CP was given until viraemia disappeared ([name], unpublished data). Moreover, mortality was 0/6, 0/18 and 6/10 in patients who were not viraemic when treated, patients who were treated until viraemia disappeared and patients in whom viraemia continued despite treatment, respectively. The last group consisted of patients in whom treatment was stopped due to AEs, lack of CP or because they were part of the initial phase I study in which only one dose was given. Patients with viraemia may thus benefit from CP and can be identified early prior to development of severe COVID-19.

### Rationale

CP has been shown to be safe and effective for treatment of several diseases. Data indicate that it is safe for treatment of COVID-19. Preliminary data indicate that treatment should be given early prior to development of severe illness. A group at high risk of severe disease and death that has the most to benefit from CP can be easily identified by detection of viraemia on admission.^19^ Phase II study data indicate that treatment should be given until SARS-CoV-2 is no longer detected in serum and the donor antibody neutralisation titres should be ≥1/640. A randomised controlled trial in which patients with viraemia are treated with CP with the equivalent of an antibody titre ≥1/640 is thus required to determine if CP can be an effective COVID-19 treatment.

### Objective

The aim is to assess the efficacy, safety and tolerability of CP for treatment of patients with COVID-19 and viraemia.

## Methods and analysis

### Study design

A multicentre, open 2:1 randomised controlled clinical trial conducted in Sweden. Study sites include Karolinska University Hospital, Danderyd Hospital and the Hospital in Falun (for a complete list of study sites, visit ClinicalTrials.gov). All Hospitals with infectious diseases departments in Sweden have been invited to participate. The study will be conducted in accordance with the Helsinki Declaration on ethical principles for medical research involving human subjects. The study is expected to take place during 2021 (3 December 2020 to 1 February 2022). This study protocol is prepared using the Standard Protocol Items: Recommendations for Interventional Trials guidelines.^21^

### Participants

Patients with COVID-19 admitted to a study hospital will be considered for study entry. Patients will be identified by notification among doctors at the hospitals. Patients will be informed of the study and offered to participate if they match the inclusion and exclusion criteria. An electronic (REDCap, a web-based service for electronic data collection) case record form will be filled in for all screened and included patients. On inclusion, an informed consent form will be signed. Enrolment of patients is done by dedicated physicians and expected to take place during a 12-month period. Intervention is taking place up to a maximum of 10 consecutive days and follow-up will be on day 28 and day 60 after inclusion (table 1). Adherence to study protocol will be monitored by registry linkages with the patient registry.

**Table 1 T1:** Planned questionnaire and sampling follow-up

Time point (days)	Prior to or on inclusion	Daily during treatment	28	60
Informed consent	X			
CRF (Case Record Form)	X	X	X	X
Routine blood chemistry	X			
Serum sample	X	X		
Virus PCR in blood	X	X		

### Eligibility criteria

Inclusion criteria for participants:

Age ≥18.Admitted to a study hospital.Active COVID-19 defined as symptoms+SARS-CoV-2 identified from upper or lower airway samples and blood.Negative pregnancy test taken before inclusion and use of an acceptable effective method of contraception until treatment discontinuation if the participant is a woman of childbearing potential.Written informed consent after meeting with a study physician and ability and willingness to complete follow-up.

Exclusion criteria for participants:

No matching plasma donor (exact matching in the ABO blood group system is required).Unavailability of plasma.Estimated glomerular filtration rate <30 (kidney failure stage III or more).Pregnancy (urinary hcg (human chorionic gonadotropin)).Breast feeding.Inability to give informed consent.

The study will be conducted at wards in study hospitals where patients with COVID-19 are treated. To be eligible to participate, the personnel involved in the study will receive appropriate training relevant to the study.

### Intervention

Patients will be randomised 2:1 to treatment with CP plus standard care or standard care only. Randomisation is by random permutated blocks using REDCap or equivalent.

Participants will receive 200 mL CP daily until SARS-CoV-2 is no longer detectable in the blood up to a maximum of 10 CP infusions. CP will be given as a slow infusion over 2 hours. CP neutralisation titre of ≥1/640 (which is higher than conventionally used as high-titre plasma) or an ELISA reactivity against the Spike protein of SARS-CoV-2 by the Euroimmun commercial assay >9 is desired. The in-house neutralisation test is performed as described.^22^

New antibody tests are under development and can be used instead if equivalence to neutralisation or Euroimmun ELISA is demonstrated. If no high-titre plasma is available, lower antibody titre plasma may be given but must in no instance be lower than 4 in the Euroimmun ELISA. CP will be obtained from respective study sites blood bank. If this is not possible, CP will be available from the Department of Clinical Immunology and Transfusion Medicine at Karolinska University Hospital.

Patients will be monitored for AEs, especially allergic reactions and impaired renal function. Patients not able to receive study treatment will receive standard care.

If an attending physician assesses that a patient is suffering from an AE induced by the plasma infusion and requiring treatment, the infusion will be stopped for that patient. The outcome will be classified as an AE necessitating treatment stop.

A study subject can terminate his/her participation in the study at any time without giving a reason why. Should a subject wish to do so, he/she will be treated in line with standard recommendations.

Study organisers can end a patient’s participation for safety reasons.

### Outcomes

Primary endpoint: mortality by day 28 after inclusion into the study.

Secondary endpoints:

Mortality by day 60 after inclusion into the study.Requirement of invasive ventilation or PaO_2_/FiO_2_ ≤70 for ≥12 hours in the case of patients not eligible for intensive care.AEs.Dose of plasma needed to clear viraemia.Time to clearance of viraemia.

### Sample size

Available data indicate that CP is safe and that high-titre CP can reduce mortality by approximately 30%. For that reason, a 2:1 randomisation is preferred. Randomisation will be done by computer-generated random numbers. Based on the available data, we assume 85%–88% survival in the control arm. Assuming a power of 80% and an alpha of 0.05%, 920 patients need to be enrolled.

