### Data analysis plan

Efficacy outcomes will be determined using Cox regressions analyses, non-parametric regression analyses and survival analyses of the cohort of patients that fulfilled entry criteria but not exclusion criteria. A per-protocol and intention-to-treat analysis will be done. Final analysis will include a description of included participants, proportions of AEs and any serious AEs, the proportion of participants withdrawn or lost to follow-up, the cumulative success and failure rates by day 28 and day 60. Categorical variables will be compared using the χ^2^ test or Fisher’s exact test and continuous variables using quantile regression. The final data analysis will be performed when a total number of 88 outcome events have occurred. An interim analysis will be performed after 44 outcome events.

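### The 88-death trigger for the final analysis agrees with the 920-patient target only at 88% control survival, and neither gives the stated 80% power at the plan's own mortality rates

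*Protocol article*

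**What the plan says.** The Sample size section of the protocol article supposes that "high-titre CP can reduce mortality by approximately 30" per cent and continues: "Based on the available data, we assume 85%–88% survival in the control arm". No source is named for the survival range. The section concludes: "Assuming a power of 80% and an alpha of 0.05%, 920 patients need to be enrolled". Under Intervention: "Patients will be randomised 2:1 to treatment with CP plus standard care or standard care only". The Abstract rounds the target: "approximately 600 participants will be enrolled to the CP therapy arm and 300 participants to the control arm".

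The Data analysis plan ties the end of the trial to a death count, not to enrolment: "The final data analysis will be performed when a total number of 88 outcome events have occurred". It places an interim look at 44 events.

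The eligibility criteria admit only patients with virus in the blood as well as the airway. For such patients the Introduction reports an "eightfold increased risk of death", and for the phase I/II patients it says "mortality was 0/6, 0/18 and 6/10 in patients who were not viraemic when treated". That sentence lists three groups in order: not viraemic (0/6), treated until viraemia cleared (0/18), and viraemia continuing despite treatment (6/10).

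**The concern.** Two rules decide when the trial is complete: a patient target and an event count. They agree only if the mortality rate is the one that links them. The plan gives a range of control survival, so the first question is whether the rules agree across that range.

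The second question is how secure the range is. The only death counts for viraemic patients in the article are 0/18 and 6/10. Together they give 6/28, or 21.4% mortality, in patients who had all received some plasma. The plan assumes 12%–15% mortality without plasma. If the true rate is higher than assumed, 88 deaths arrive well before 920 patients and the two rules give quite different trials. What is at stake is when the trial ends, how many patients it has by then, and what power the sponsor believes it has.

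**Working it through.** **Inputs.** Control mortality p of 12%–15% (from 85%–88% survival), a 30% reduction read as a risk ratio of 0.70, 2:1 allocation, 920 patients (307 control, 613 plasma) and 88 events. My assumptions:
- An outcome event is a death by day 28; the article does not define the term.
- The alpha is 0.05 two-sided. It is printed with a percent sign, and sidedness is not stated.
- There is no dropout.

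**Origin of the 88.** The pooled death rate is (p + 2 × 0.7p)/3 = 0.8p. At p = 12% this is 9.6%, and 920 × 0.096 = 88.3 deaths. At 900 patients it is 86.4. The derivation of 88 is not printed, but it fits 920 patients at 88% control survival.

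**The 80% power.** The two-proportion formula for 80% power needs 1,899 patients at 15% control mortality and 2,442 at 12%. One-sided, it needs 1,500 and 1,932. Reading the alpha literally as 0.05% raises the number further (5,745 at 12%, two-sided). No variant tried reproduces 920.

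**Pilot rate.** 6/(18 + 10) = 21.4%, exact 95% CI 8.3% to 41.0%. Read as the control rate, p = 21.4%. Read as the plasma-arm rate, p = 21.4%/0.7 = 30.6%.

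**Timing and power.** Patients at 88 deaths = 88/(0.8p). Deaths at 920 = 920 × 0.8p. Power = Φ[(0.3p − 1.96 × SE0)/SE1], where SE0 is the standard error under the pooled rate and SE1 the standard error under the two separate rates. At p = 12% and 307/613 patients, SE0 = 0.0206 and SE1 = 0.0217, so power = Φ[(0.036 − 0.0404)/0.0217] = 42%.

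| Control mortality | Plasma mortality | Patients at 88 deaths | Power at 88 deaths | Deaths at 920 | Power at 920 |
|---|---|---|---|---|---|
| 12% | 8.4% | 917 | 42% | 88 | 42% |
| 15% | 10.5% | 733 | 43% | 110 | 51% |
| 21.4% | 15.0% | 513 | 45% | 158 | 68% |
| 30.6% | 21.4% | 359 | 48% | 225 | 85% |

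If both arms had 21.4% mortality, 88 deaths would come at 411 patients. The Data analysis plan also names Cox regression. For a hazard ratio of 0.70, 88 events give about 35% power by the Schoenfeld formula (two-sided 0.05, 2:1), and about 278 events are needed for 80%.

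**Pilot against the assumption.** The chance of 6 or more deaths in 28 is 0.11 at 12% and 0.24 at 15% (assumed control rates). It is 0.026 at 8.4% and 0.067 at 10.5% (implied plasma rates).

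**The case against.** A reader might infer that the pilot shows 85%–88% to be wrong, and that the trial would therefore end at about half its size. The documents do not support this, for four reasons.

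- **The interval is wide.** It runs from 8.3% to 41.0% and contains both the assumed control rates and, at its low end, the implied plasma rates. At its lower limit, read as plasma-arm mortality, 88 deaths come at about 928 patients, so the timing would not shift at all. At its upper limit, read the same way, they come at about 188.
- **The 28 patients represent neither arm cleanly.** They are grouped by what happened after treatment. All six deaths fall in the group whose plasma was stopped for adverse events or lack of supply, or who got a single dose in phase I. Follow-up time is not given. So it does not follow that untreated viraemic patients must die at 21% or more.
- **The eightfold risk has no baseline.** A baseline of 1.5%–1.9% would give 12%–15% (12/8 and 15/8). The article neither supports nor excludes that, and the full protocol may give the source of the rate.
- **A higher death rate costs no power at the trigger.** Power at 88 deaths rises slightly, from 42% to 48%. Reaching a fixed event count with fewer patients is how an event-driven design should behave.

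All four points stand, and they limit what the pilot can be used for. They leave untouched the mismatch within the plan's own range (917 against 733 patients) and the gap between the stated and recomputed power. What a higher rate would change is the power forgone by ending at 88 deaths: 45% instead of 68%, or 48% instead of 85%, had the 920 been completed.

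**Conclusion.** The point holds as a mismatch between two rules and an overstated power. The 88-event trigger and the 920-patient target agree at 88% control survival and at no other rate in the stated range. At 85% survival the trigger comes about 187 patients early (920 − 733). At mortality near the pilot's it could come at about 360 to 515 patients, but the pilot makes this only plausible; it does not establish it.

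Power for a 30% reduction is 42%–48% at 88 deaths. At 920 patients it is 42%–51% under the plan's own rates and 68%–85% at 21%–31% control mortality. The 80% in the Sample size section is therefore unsupported at 12%–15%, and whether 920 is adequate depends largely on the control rate. These figures rest on a risk ratio of 0.70, 2:1 allocation, two-sided 0.05, deaths by day 28 as the counted events, and no dropout.

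**What to change.** **Abstract and Sample size.** Give the control mortality with an interval for viraemic patients and say where it comes from. Replace the 80% power statement with expected deaths and power at 920 patients for control mortality of about 12%, 15%, 21% and 31%, as in the table above.

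**Data analysis plan.** Reconcile the trigger with the enrolment target. Time the final analysis on completed 28-day follow-up of the planned 920 patients instead of a fixed 88 deaths. Restate the 44-event interim to match, and align it with the looks at 100, 300 and 600 patients listed under Ethics and dissemination. Monitor pooled mortality blind to arm, so that the assumption is checked without revealing the treatment effect. The event counts should not simply be deleted, because that would leave this section without a timing rule.

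**Cost.** A paragraph, a small table and no patients beyond 920. The final analysis may come later than 88 deaths, and the stated power becomes less favourable. The change does not supply the missing power: at 12%–15% control mortality, 920 patients still give 42%–51%.

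### The planned 920 patients and 88 deaths give about 35–51% power for a 30% mortality reduction, not the stated 80%, and alpha is printed as 0.05%

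*Protocol article*

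**What the plan says.** The Sample size section takes a mortality reduction of about 30% as the plausible effect of high-titre plasma, chooses 2:1 randomisation, and adds "we assume 85%–88% survival in the control arm". It concludes: "Assuming a power of 80% and an alpha of 0.05%, 920 patients need to be enrolled".

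Three other places depend on this calculation:

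- The Abstract (Methods and analysis) repeats the effect and survival assumptions and says "approximately 600 participants will be enrolled to the CP therapy arm and 300 participants to the control arm".
- The strengths and limitations list says "Powered to detect a 30% mortality decrease".
- The Data analysis plan names Cox regression and survival analyses for efficacy and says "The final data analysis will be performed when a total number of 88 outcome events have occurred", with an interim analysis at 44 events.

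The primary endpoint is mortality by day 28. The article does not state the formula, the sidedness of the test or any allowance for dropout.

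**The concern.** With a control mortality of only 12–15%, a 30% relative reduction is an absolute difference of 3.6 to 4.5 percentage points. Detecting a difference that small with 80% power usually takes well over a thousand patients, so 920 looked too few. Eighty-eight deaths also looked too few for a hazard ratio near 0.70.

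What is at stake is how a null result would be read. If the trial reports no significant difference and is described as powered for a 30% reduction, readers will conclude that plasma does not achieve such a reduction in viraemic patients. If true power is nearer 40%, that conclusion is not supported.

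**Working it through.** **Inputs (protocol article).** Control mortality p0 = 0.12 to 0.15 (from 88% and 85% survival); 30% reduction; allocation 2:1; power 80%; N = 920; final analysis at 88 deaths. The reduction must be relative, because an absolute drop of 30 points from 12–15% is impossible. Treated mortality p1 = 0.7 × p0, which is 0.084 to 0.105. Alpha is taken as two-sided 5% (assumed).

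**Step 1. Try to reproduce 920.** The pooled-variance formula for two proportions, with n controls and 2n treated, is

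n = [1.96·A + 0.842·B]² / (p0 − p1)²

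where A = √(1.5·p̄(1 − p̄)), B = √(p0(1 − p0) + p1(1 − p1)/2) and p̄ = (p0 + 2p1)/3.

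- 12% vs 8.4%: p̄ = 0.096, A = 0.3608, B = 0.3796. n = [(0.7072 + 0.3195)/0.036]² ≈ 813.2, rounded up to 814 controls. Total 3 × 814 = **2,442**.
- 15% vs 10.5%: p̄ = 0.12, A = 0.3980, B = 0.4177. n = [(0.7801 + 0.3516)/0.045]² ≈ 632.4, rounded up to 633 controls. Total 3 × 633 = **1,899**.

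920 is not reproduced. Other readings do not reach it either:

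| Reading | Total N for 80% power |
|---|---|
| Two-sided 5%, continuity-corrected | 1,998–2,565 |
| One-sided 5% | 1,500–1,932 |
| One-sided 5%, 1:1 allocation | 1,358–1,746 |
| Alpha 0.0005 as printed, two-sided | 4,470–5,745 |

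Reading the 30% as a hazard ratio or odds ratio of 0.70 raises the number needed.

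**Step 2. Power with 920 patients** (about 307 controls and 613 treated): power = Φ{[√n·(p0 − p1) − 1.96·A]/B}, with n = 920/3 = 306.7 and √n = 17.51.

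- 12%: (0.6304 − 0.7072)/0.3796 = −0.202, so power is **42%**.
- 15%: (0.7881 − 0.7801)/0.4177 = 0.019, so power is **51%**.

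With the 900 patients of the Abstract it is 41–50%. With a one-sided 5% test and 920 patients it is 54–63%. At the printed alpha of 0.0005, two-sided, it is 5–8%.

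**Step 3. The 88-event trigger.** Schoenfeld's formula for a log-rank or Cox test, with one third of patients in the control arm, gives

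events = (1.96 + 0.842)² / [(1/3)(2/3)(ln 0.70)²] = 7.849 / (0.2222 × 0.1272) ≈ **278**.

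With 88 events: √(88 × 2/9) × |ln 0.70| = 4.422 × 0.3567 = 1.577. Power = Φ(1.577 − 1.960) = Φ(−0.383) = **35%**. A one-sided 5% test gives 47%. Freedman's method gives about 252 events needed and 38% power at 88.

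**Step 4. Where 88 may come from.** Expected deaths among 920 patients at 12% and 8.4% are 306.7 × 0.12 + 613.3 × 0.084 = 36.8 + 51.5 = 88.3. So 88 matches the deaths expected in 920 patients at the low end of control mortality. The two figures agree with each other, but neither delivers 80% power. At 15% control mortality, overall mortality is 12% and 88 deaths would arrive after about 88/0.12 = 733 patients.

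**Step 5. What the design can detect with 80% power** (two-sided 5%). With 920 patients it needs a risk ratio of about 0.54 (12% control mortality) or 0.58 (15%), a reduction of 46% or 42%. With 88 events it needs a hazard ratio of exp(−2.802/4.422) = 0.53.

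**The case against.** The central mismatch is hard to dispute, because the inputs and the result stand together in one section. Nor is it a matter of journal condensation: the article states a figure that its own assumptions contradict. The fair objections concern the edges.

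- **Effect measure.** The article speaks of a mortality reduction, not a hazard ratio. A risk ratio of 0.70 at 12–15% mortality corresponds to a hazard ratio of about 0.683–0.686, and 88 events then give 38–39% power. This stands: the 35% applies if 30% is read as a hazard ratio of 0.70. It does not alter the conclusion.
- **A true effect more likely missed than found.** With 920 patients and 15% control mortality, power is 51%, an even chance. This stands for that single scenario. The article, however, ties the final analysis to 88 events, and there the statement holds under every reading above that uses a two-sided 5% test.
- **Alpha.** 0.05% is very probably a slip for 0.05, and sidedness is not given, so two-sided 5% is an assumption. This stands, but a one-sided 5% test still falls well short of 80%.
- **Origin of 88.** The article does not explain it. The match with 88.3 expected deaths is an inference and holds only at 12% control mortality.
- **900 against 920.** The Abstract says approximately, so this is rounding, and power barely changes.

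**Conclusion.** The concern holds. On the article's own inputs, 920 patients give 42–51% power and 88 deaths give 35% (38–39% if a risk ratio of 0.70 is converted to a hazard ratio), against a stated 80%. Reaching 80% would take roughly 1,900 to 2,440 patients, two to two and a half times the plan, or about 278 deaths, three times the plan.

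These figures assume a two-sided 5% test, 2:1 allocation, no dropout and no alpha spent at interim looks. Dropout or alpha spending would lower power further. The statement that the trial is powered for a 30% reduction is wrong as written, and because it concerns the primary endpoint it must be corrected.

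**What to change.** 1. In the Sample size section, correct alpha to 5% and state that the test is two-sided, if that is what was intended.
2. Replace the power statement, for example: with a two-sided 5% test, 920 patients give 42–51% power for a 30% relative reduction at 12–15% control mortality, and 80% power for a reduction of 42–46%; 88 deaths give 35% power at a hazard ratio of 0.70 and 80% power at 0.53.
3. Remove or reword the power claim in the strengths and limitations list.
4. State that interpretation will rest on the confidence interval and that a non-significant result does not exclude a 30% reduction.
5. For tidiness, use one total (900 or 920) throughout.

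The cost is a text correction in the protocol, and in the registration if it carries the same statement. No extra patients are needed, but the stated power becomes less favourable. If the sponsor wants to keep 80% power for a 30% reduction, it would have to raise the enrolment and event targets to the figures above. If it believes a reduction of 42–46% is realistic, it should say so and justify it.
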